## 1.8 **Summary**

This protocol is to test the safety and immunologic effects of adding systemic administration of CDX-1127 to cancer vaccines. The study design will provide data on safety of adding CDX-1127 to a vaccine regimen, and will provide preliminary data on the immunologic effects of that combination. The vaccine regimen consists of the 6MHP vaccine + Montanide ISA-51 + polyICLC.

Patients in either study arm will be randomized to receive varilumab or not.

This clinical trial will incorporate immunologic studies of immune responses in blood during the vaccine regimen and also at 6 months, when there will be specific assessment of memory responses to each vaccine. This study will provide first-in-humans data on the impact of CD27 agonism in combination with a vaccine. The study holds promise to optimize the immunogenicity of vaccines comprising class II MHC peptides with either of two improved adjuvant systems, which may have relevance across a spectrum of cancers.

## 2.0 **OBJECTIVES**

### 2.1 **Primary Objectives**

- 1) **Safety**: To test the safety of CDX-1127 administered concurrently with a melanoma vaccine (6MHP). The melanoma vaccine will include Montanide ISA-51 and will be co-administered with polyICLC.

Safety will be evaluated by adverse event assessments, including CTCAE v5.0 and sub-classified by irAE categories. [Endpoint: dose-limiting toxicities (DLTs) based on CTCAE v5.0 treatment related adverse events]

- 2) **Immunogenicity**: To determine whether addition of CD27 antibody to a melanoma vaccine improves the persistence of CD4+ Th1 responses to vaccine antigens. [Endpoint: CD4+ responses to 6MHP (by ELISpot), measured as the percent of patients with persistent responses (pRsp) at either day 127 or day 176, or both].

### 2.2 **Secondary Objectives**

- 1) To assess whether CD27 antibody decreases regulatory T cells (FoxP3+ cells) in the vaccine site microenvironment at weeks 3 and 12. [Endpoint: in vaccine site biopsies FoxP3+ CD4+ T cells per mm^2 in by immunohistochemistry and gene expression analysis)] **Note**: with revision to reduce ulceration at vaccine sites, biopsies are not required at week 12 for participants whose week 12 visit would be due after IRB approval of Protocol v12-03-2020.
- 2) To determine whether addition of CD27 antibody to a melanoma vaccine,
  - a) Decreases circulating regulatory T cells [Endpoint: circulating Tregs, % of CD4+ T cells responding to vaccine antigens; FoxP3+ CD4+ T cells as measured by flow cytometry]
  - b) Improves the frequency of CD4+ Th1 responses to vaccine antigens [Endpoint: CD4+ response to 6MHP measured by ELISpot; maximum increase after vaccination at any time point]
  - c) Improves the frequency of durable CD4+ Th1 responses to vaccine antigens (dRsp) [Endpoint: CD4+ response to 6MHP measured by ELISpot; at two

- consecutive time points (day 8 to 85)]
- d) Increases the CD4+ Th1 memory response (mRsp) to vaccine antigens at 6 months. [Endpoint: CD4+ response to 6MHP by ELISpot a week after booster vaccine on day 176]

## 2.3 **Exploratory Objectives**

- 1) To assess the impact of CD27 antibody on induction of
  - a. Antibodies to helper peptides in 6MHP (assessed in serum by ELISA for IgG). [Endpoint: IgG antibodies to 6MHP]
  - b. CD8+ T cell responses to melanoma antigens in the vaccine, or to other antigens by epitope spreading. [Endpoint: rate of CD8+ T cell responses to peptides not in vaccine]
  - c. CD4+ T cell activation versus exhaustion. [Endpoint: proportion of CD4+ and CD8+ T cells that express PD-1, TIM-3, LAG-3, TIGIT with respect to HLA-DR as an activation marker by flow cytometry]
- 2) To obtain preliminary estimates of disease-free survival (DFS) and overall survival.

## 3.0 **PARTICIPANT SELECTION CRITERIA**

### 3.1 **Inclusion Criteria**

- 1) Either of the following patient populations may be eligible:
  - a. Patients with stage IIB, IIC, III, or IV cutaneous, mucosal, or unknown primary melanoma at original diagnosis or at restaging after recurrence, rendered clinically free of disease by surgery, other therapy, or spontaneous remission, within 6 months prior to registration. Patients with high-risk stage IIA cutaneous melanoma (by DecisionDx Melanoma test, Castle Biosciences, Inc., Friendswood, TX) also may be eligible.
  - b. Patients with stage IIB, IIC, III, or IV uveal melanoma at original diagnosis or at restaging after recurrence, rendered clinically free of disease by surgery, other therapy, or spontaneous remission within 6 months prior to registration. Patients with uveal melanoma treated definitively with plaque therapy may also be eligible if treated within 6 months prior to registration. Patients with high-risk stage IIA uveal melanoma (Class 2 DecisionDX-UM Melanoma test, Castle Biosciences, Inc., Friendswood, TX) also may be eligible.
- 2) Patients with small radiologic or clinical findings of an indeterminate nature may still be eligible: examples include a new 5 mm lung nodule that is too small to characterize or an asymptomatic 12 mm bony lucency that is not classic for malignancy, where clinical care may otherwise be to follow the patient with repeat imaging rather than to treat the lesion.

Participants may have had cutaneous, uveal, mucosal primary melanoma, or an unknown primary melanoma. Diagnosis of melanoma must be confirmed by cytological or histological examination. Staging of cutaneous melanoma will be based on version 8 AJCC staging system ([Section 9.2](#)). Patients with primary uveal melanoma that are considered high-risk by DecisionDX-UM will not require pathologic review.

- 3) Participants will be required to have radiological studies to rule out radiologically evident melanoma metastasis. Required studies include:
  - Chest CT scan,

- Abdominal and pelvic CT scan, and
  - Head CT scan or MRI
  - PET/CT fusion scan may replace scans of the chest, abdomen, and pelvis.
- 4) Participants who have had brain metastases will be eligible if all of the following are true:
- Each brain metastasis must have been completely removed by surgery or each unresected brain metastasis must have been treated with stereotactic radiosurgery.
  - No brain metastasis is > 2 cm in diameter at the time of registration.
  - Any neurologic symptoms attributable to brain metastases have returned to baseline.
  - There is no evidence of new or enlarging brain metastases.
- 5) The most recent surgical resections or gamma-knife therapy for malignant melanoma must have been completed  $\geq 1$  week and  $\leq 6$  months prior to registration.
- 6) ECOG performance status of 0 or 1 ([Section 9.3](#)).
- 7) Ability and willingness to give informed consent.
- 8) Laboratory parameters as follows:
- ANC > 1000/mm^3
  - Platelets > 100,000/mm^3
  - Hgb > 9 g/dL
  - HgbA1c  $\leq 8.5\%$
  - AST and ALT  $\leq 2.5$  x upper limits of normal (ULN)
  - Bilirubin  $\leq 2.5$  x ULN (except in patients with Gilbert's disease, where bilirubin to 4x ULN is allowed)
  - Alkaline phosphatase  $\leq 2.5$  x ULN
  - Creatinine  $\leq 1.5$  x ULN
- 9) Age 18 years or older at registration.
- 10) Participants must have at least one intact (undissected) axillary and/or inguinal lymph node basin.

### **3.2 Exclusion Criteria**

- 1) Participants who have received the following medications or treatments at any time within 4 weeks of registration:
- Chemotherapy
  - Interferon (e.g. Intron-A®)
  - Radiation therapy (Stereotactic radiotherapy, such as gamma knife, can be used  $\geq 1$  week and  $\leq 6$  months prior to registration)
  - Allergy desensitization injections
  - High doses of systemic corticosteroids, with the following qualifications and exceptions:
    - In patients with adrenal or pituitary insufficiency replacement steroid doses are allowed; however, daily doses of 10 mg or more of prednisone (or equivalent) per day administered

- parenterally or orally are not allowed in patients with normal adrenal and pituitary function.
- Inhaled steroids (e.g.: Advair®, Flovent®, Azmacort®) are permitted at low doses (less than 500 mcg fluticasone per day, or equivalent) .
  - Topical, nasal, and intra-articular corticosteroids are acceptable.
  - Growth factors (e.g. Procrit®, Aranesp®, Neulasta®)
  - Interleukins (e.g. Proleukin®)
  - Any investigational medication
  - Targeted therapies specific for mutated BRAF or for MEK
- 2) Participants who are currently receiving nitrosoureas or who have received this therapy within 6 weeks of registration.
  - 3) Participants who are currently receiving a checkpoint molecule blockade therapy, or who have received this therapy within 12 weeks of registration.
  - 4) Participants with known or suspected allergies to any component of the vaccine.
  - 5) Participants who were vaccinated previously with 6MHP are excluded. Participants who have received vaccinations containing agents other than the synthetic peptides included in this protocol and have recurred during or after administration of the vaccine will be eligible to enroll 12 weeks following their last vaccination.
  - 6) Participants who have previously received CDX-1127 or other CD27 agonistic antibody.
  - 7) Pregnancy. Female participants of childbearing potential must have a negative pregnancy test (urinary or serum beta-HCG) obtained within 2 weeks prior to registration. Males and females must agree, in the consent form, to use effective birth control methods during the course of active study treatment and for up to 70 days after the last dose of study treatment.
  - 8) HIV positivity or evidence of active Hepatitis C virus (testing to be done within 6 months of study entry).
  - 9) Female participants must not be breastfeeding.
  - 10) Participants in whom there is a medical contraindication or potential problem in complying with the requirements of the protocol in the opinion of the investigator.
  - 11) Participants classified according to the New York Heart Association classification as having Class III or IV heart disease ([Section 9.4](#)).
  - 12) Participants with uncontrolled diabetes, defined as having an HgbA1c > 8.5%.
  - 13) Participants must not have had prior autoimmune disorders requiring cytotoxic or immunosuppressive therapy, or autoimmune disorders with visceral involvement. Participants with an active autoimmune disorder requiring these therapies are also excluded. The following will not be exclusionary:
    - The presence of laboratory evidence of autoimmune disease (e.g. positive ANA titer) without symptoms
    - Clinical evidence of vitiligo
    - Other forms of depigmenting illness
    - Mild arthritis requiring NSAID medications

- Resolved childhood asthma/atopy
- Intermittent use of bronchodilators or local steroid injections
- Hypothyroidism stable on hormone
- Replacement for Addison's disease

14) Participants with known addiction to alcohol or drugs who are actively taking those agents, or participants with recent (within 1 year) or ongoing illicit IV drug use.

15) Participants who have received a live vaccine within 30 days of registration.

16) Body weight < 110 pounds at registration, due to the amount and frequency with which blood will be drawn.

17) Participants with prior autoimmune pneumonitis.

### **3.3 Registration and Randomization**

All participants must sign the consent form prior to determination of eligibility for this study. All participants who meet the inclusion/exclusion criteria may be registered. Registration will occur following verification of eligibility by the treating physician. Participants should receive their first study treatment within 3 weeks of registration.

When a site is ready to enroll a patient, the following documentation must be scanned and emailed to the UVA Coordinating Center (UVA CC):

- Patient and staff signed informed consent form (ICF)
- Completed Inclusion/Exclusion checklist demonstrating participant eligibility
- Supporting documentation needed to confirm eligibility (lab results, scan results etc.)

Consult the Manual of Operations for instructions on sending this information. The Coordinating Center will consult with the Sponsor if questions arise in confirming eligibility. The UVA CC will communicate the participant number and treatment dose assignment to the enrolling site.

Registration will occur following verification of eligibility by the treating physician.

Participants who are consented and accrued to the study should be registered in OnCore in accordance with the Clinical Trial Management System Policy via the UVA OnCore Resources link in Oncore. General guidelines are available in the OnCore User Manual and Data Entry Guide.

Treatment randomization will be discussed with participants during the process of informed consent. Treatment randomization will be based upon the study design as shown in [Figure 1](#), until a safety bound has been triggered or target accrual has been met. The randomization sequence will be generated by the study statisticians. Randomization will occur after registration within 1 week of the start of treatment.

This study does not involve any blinding or masking procedures. Participants will be told the treatment they are receiving.

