### **5.7 Replacement of Study Participants**

A participant who is enrolled but does not receive study drug or does not undergo any of the study related procedures may be replaced. Every attempt will be made to evaluate any data from these participants for endpoint assessment.

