### **6.4 Clinical Labs**

Laboratory tests for hematology, chemistry, urinalysis, and other are specified in [Table 8](#). Pre-dose laboratory procedures can be conducted up to 72 hours prior to dosing. Results must be reviewed by the investigator or qualified designee and found to be acceptable prior to each dose of varlilumab. Any abnormal laboratory values captured which are not included in [Table 8](#) but are considered to be pertinent positive clinical signs/symptoms, and laboratory results obtained as part of routine care of patients will be recorded in the UVA Cancer Center database and reported as described in [Section 8.6.1](#). If there is any doubt on the part of study personnel concerning what constitutes a pertinent positive finding, the PI and sponsor will be consulted.

| Table 8: Clinical Labs |                                                 |                                         |                                                                          |
|-------------------------------|-------------------------------------------------|-----------------------------------------|--------------------------------------------------------------------------|
| Hematology             | Chemistry                                | Urinalysis                       | Other                                                             |
| Hematocrit                    | Albumin                                         | Blood                                   | Serum $\beta$ -human chorionic gonadotropin ( $\beta$ -hCG)  |
| Hemoglobin                    | Alkaline phosphatase                            | Glucose                                 | ANA                                                                      |
| Platelet count                | Alanine aminotransferase (ALT)                  | Protein                                 | Rf                                                                       |
| WBC (total and differential)  | Aspartate aminotransferase (AST)                | Specific gravity                        |                                                                          |
| Red Blood Cell Count          | Carbon Dioxide (CO 2 or bicarbonate) | Microscopic exam ( If abnormal ) | Blood for correlative studies: Section 6.9 .             |

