## 7.1 **Evaluation of Sample Populations and Endpoints**

### 7.1.1 **Safety**

All participants receiving any protocol defined treatment will be evaluated for safety.

The 6MHP vaccine has been safe, with lower toxicities than with class I peptides, in particular with lower autoimmune or hyperimmune toxicities. Data from MEL63 indicates a DLT rate of 6.3% with a 95% CI(1, 18%). Reported DLT information (ref: Burris et al JCO May 2) for CDX-1127 in patients with advanced solid tumors indicated a DLT rate of 4% with a 95% CI(<1, 20%). We do not anticipate increased toxicities by combining 6MHP vaccine with CDX-1127 therefore, this trial will be designed with stopping rules for DLT rates beyond those expected with vaccine alone or CDX-1127 alone. Formal safety bounds based upon monitoring dose limiting toxicities (DLT) ([Section 8.9](#)) will guide decisions about early stopping due to potential safety concerns. If a stopping bound is crossed then accrual to the study will be suspended until the study PI, co-investigators and the DSMC can review the data, and determine if the study should continue, be amended or be closed to further accrual.

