### 7.1.2 **Immunogenicity**

All eligible participants receiving any protocol defined treatment who have at least two evaluable blood draws (including baseline) for immune analyses will be evaluated for the following immune response parameters. In addition, all

participants are considered 'evaluable' for the primary endpoint if they have been evaluated for immune response at baseline and at least day 127; or they have progressed prior to the day 127 assessment; or have stopped treatment due to DLTs.

In PBMC:

- CD4+ Th1 response to vaccine antigens by ELIspot:
  - Magnitude of response at all times
  - Frequency of response over time
  - Persistence of response over time
- Circulating regulatory T cells (Tregs) as measured by flow cytometry over time
- CD8+ T cell responses to peptides not in the vaccine over time
- CD4+ T cell activation versus exhaustion
  - Activation measured by an increase in %DR+ CD4+ cells of total CD4+ cells
  - Exhaustion measured by increase in the % of DR+CD4+ T cells that co-express both PD-1 and either LAG3 or TIM3.

In the tumor microenvironment:

- FoxP3+ CD4+ T cells per mm^2 in vaccine site biopsies by immunohistochemistry and gene expression analysis at weeks 3 and 12. **Note:** with revision to reduce ulceration at vaccine sites, biopsies are not required at week 12 for participants whose week 12 visit would be due after IRB approval of Protocol v12-03-2020.

In serum:

- IgG antibodies to 6MHP by ELISA for IgG over time

A CD4+ T cell response to 6MHP (Rsp), is defined as all of the following, based on direct ELIspot assay:

- a) an increase of at least 20 IFN-gamma secreting cells per 100,000 CD4+ T cells, over the maximum of the negative controls ( $T_{\text{neg cctrl}}$ )
- b) no overlap in standard deviations between the response to 6MHP peptide pool ( $T_{\text{vax}}$ ) and  $T_{\text{neg cctrl}}$
- c) the ratio of  $T_{\text{vax}}$  to  $T_{\text{neg cctrl}}$  at one or more time points, after week 0, is at least 5-fold the prevaccine ratio of  $T_{\text{vax}}$  to  $T_{\text{neg cctrl}}$ . Note that any prevaccine ratio of  $T_{\text{vax}}$  to  $T_{\text{neg cctrl}}$  below 1 will be set to 1 to avoid overinflating that ratio.

A durable response (dRsp) is defined as a Rsp detected over at least two consecutive time periods during vaccination (days 8 through 85).

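### The arm is assigned, unmasked, up to a week before first dose and only treated participants are analysed, so withdrawals after learning the arm leave the comparison; randomise at first dose or the day before and add an all-randomised sensitivity analysis

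*Combined protocol and SAP*

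**What the plan says.** **Timing and masking (section 3.3).** Registration follows verification of eligibility, and "Participants should receive their first study treatment within 3 weeks of registration". The arm comes later: "Randomization will occur after registration within 1 week of the start of treatment". It is open: "This study does not involve any blinding or masking procedures. Participants will be told the treatment they are receiving".

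**Who is analysed (section 7.1).** For safety: "All participants receiving any protocol defined treatment will be evaluated for safety". The immune parameters use "All eligible participants receiving any protocol defined treatment who have at least two evaluable blood draws". Section 7.1.3 limits DFS and OS to eligible, treated participants in the same way, although both run from randomisation. No all-randomised set is defined.

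**The primary immune endpoint (section 7.1.2).** Participants are evaluable for persistent response (pRsp) if they were assessed at baseline and at least day 127, or if "they have progressed prior to the day 127 assessment; or have stopped treatment due to DLTs". The last two groups count as response failures.

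**Replacement (section 5.7).** "A participant who is enrolled but does not receive study drug or does not undergo any of the study related procedures may be replaced". The next sentence promises an effort to evaluate whatever data such participants have, but section 7 gives no rule for using them.

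**The concern.** Randomisation makes the two groups comparable at the moment of assignment. Here up to seven days can pass between that moment and the first dose, with the arm known to participant and site. A participant who hoped for the antibody, or hoped to avoid it, can leave in that interval. The defined analysis sets then exclude that person, and section 5.7 allows another to be enrolled. Replacement restores the count but not the comparability.

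If those who leave differ between arms in their likely immune response, the difference in pRsp is biased. With about 15 evaluable participants per arm and a further-study criterion that turns on the sign of a lower confidence bound, very few such losses could matter.

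**Working it through.** **Inputs.** Target of 30 evaluable, 15 per arm (synopsis, Accrual Goal); 10% allowance and maximum of 34 (7.2); earlier-trial pRsp of 5/38 (7.2); criterion of an observed difference of about 28% to 31%, based on a 90% Miettinen-Nurminen interval lying above zero (7.2). Loss between randomisation and first dose is not given. I assume 0 to 4, where 4 = 34 - 30 is the whole allowance (4/34 = 11.8%), and 17 randomised per arm. Differences are Arm A (with CDX-1127) minus Arm B, using the arms of Table 9.

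**The plan's own figures reproduce.**
- 30/0.90 = 33.3, rounded up to 34.
- The exact 90% interval for 5/38 is 5.3% to 25.7%, half-width 10.2 points.
- At 15 per arm with fractional counts, the smallest difference (in 1-point steps) with a positive lower bound is 27 points at a control rate of 13.1% and 31 points at 25.7%, against the stated 28 to 31.

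**Possible bias in one arm's rate.** Let p be the arm's true rate, f the fraction lost before dosing and q the response rate those lost would have had. The rate among the treated is (p - f·q)/(1 - f). This equals p when q = p, so loss unrelated to response gives no bias. For losses all in one arm of 17, with non-responders lost (q = 0):
- p = 13.1%: one lost gives 13.1 × 17/16 = 13.9 (+0.8 points); four lost give 13.1 × 17/13 = 17.1 (+4.0).
- p = 43.1% (illustrative, 13.1 + 30): one lost gives 43.1 × 17/16 = 45.8 (+2.7); four lost give 43.1 × 17/13 = 56.4 (+13.3).

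If responders are lost instead (q = 1), the 43.1% rate falls by 3.6 points with one lost and by 17.5 with four.

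**Effect on the criterion.** The bound is the value d at which (p1 - p2 - d)/√V(d) = 1.645. V(d) is the variance at the maximum-likelihood rates constrained to differ by d, multiplied by N/(N - 1). Each row compares all randomised participants (untreated counted as non-responders) with the treated-only count.

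| All randomised | Difference, lower bound | Treated only | Difference, lower bound |
|---|---|---|---|
| 6/17 v 2/17 | 23.5, -0.8 | 6/16 v 2/17 (one lost in A) | 25.7, +0.8 |
| 7/17 v 3/17 | 23.5, -2.6 | 7/15 v 3/17 (two lost in A) | 29.0, +1.6 |
| 7/17 v 2/17 | 29.4, +4.4 | 7/16 v 2/17 (one lost in A) | 32.0, +6.4 |
| 6/17 v 2/17 | 23.5, -0.8 | 6/17 v 2/16 (one lost in B) | 22.8, -2.3 |

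In row 1 one loss changes the sign of the bound, although 25.7 is still below the stated 28 to 31. In row 2 two losses move both the bound and the observed difference across. In row 3 nothing changes. Row 4 shows that counting the untreated as failures favours Arm A when the loss is in Arm B.

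**The case against.** **The protocol already limits the window.** Eligibility is verified before registration, randomisation must fall within a week of treatment although treatment may follow registration by three weeks, and same-day randomisation is already allowed. This stands, and it makes the change a tightening of existing wording. It does not remove the week in which the arm is known.

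**The lab check as an arm-specific exclusion.** Section 6.4 requires results to be "found to be acceptable prior to each dose of varlilumab", and only Arm A receives varlilumab, so a reader might infer that this check removes Arm A participants. The documents do not support that. The check governs varlilumab, both arms are scheduled for vaccine on Day 1, and section 7.1 asks only for some protocol treatment. An Arm A participant who is vaccinated while varlilumab is held counts as treated. What remains is withdrawal after learning the arm.

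**No analysis can repair the loss.** This is also tempting, because the first research blood in both calendars is on Day 1 and an untreated participant would normally have no immune data. But section 7.1.2 already counts progressors and DLT stops as failures without an assay, and the same can be done here. DFS and OS need no assay at all.

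**Untreated participants leave every set without exception.** That is slightly too strong. The evaluability wording in 7.1.2 could be read to count an untreated participant who progressed before day 127, and section 5.7 states an intention to use any available data. Neither is a rule for someone who simply withdraws.

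**Fragility is not bias.** At 15 per arm, 7/15 v 2/15 has a lower bound of +5.6 and 6/15 v 2/15 has -0.4, so one might say a single replacement decides the trial. That requires the person lost and the replacement to have opposite outcomes in the same arm, and section 7.3 contains no within-arm replacement. Adding one untreated Arm A non-responder to the first example gives 7/16 v 2/15, with a bound of +3.3, still positive. The objection is right that such figures show sensitivity near the threshold, not the size of this bias.

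**Conclusion.** The concern holds in a limited form. Open assignment up to a week before dosing, treated-only analysis sets and permitted replacement together let arm-driven withdrawals disappear from the comparison, and no rule restores an all-randomised one. Near the further-study criterion, one untreated Arm A participant can change the sign of the lower bound, and two can move both the bound and the observed difference across.

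The size rests on assumptions: 0 to 4 losses, 17 randomised per arm, losses concentrated in one arm, and a link between withdrawal and immune response that the documents neither show nor exclude. With no losses, or losses unrelated to response, the bias is zero. A reader might also infer that Day 1 randomisation would remove nearly all of the problem. That share cannot be derived without a pre-dose loss rate, and refusal after disclosure at the visit remains possible. Exclusions after the first dose are a separate matter.

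**What to change.** 1. **Section 3.3.** Replace the timing sentence with: *Randomization takes place on the day of first dose or the day before, after eligibility has been confirmed; the arm is disclosed only then.* No change to pre-dose laboratory rules is proposed.
2. **Section 7.5.** Report by arm the number randomised and not treated, with reasons.
3. **Section 7.5.** Add a sensitivity analysis of pRsp in all randomised participants, counting the untreated as non-responders. Read it as a check, not a correction, because its direction depends on which arm lost people (row 4 of the table).
4. **Sections 5.7 and 7.1.** Reconcile the stated intention to evaluate data from replaced participants with the analysis sets, and say whether an untreated participant who progresses before day 127 is evaluable.

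Item 1 helps only participants not yet randomised. The title of section 1.7 already refers to the first 15 on this trial, and the documents do not say how many remain. Items 2 and 3 also cover those already enrolled.

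The cost of item 1 is scheduling: sites must be ready for a possible varlilumab infusion at each Day 1 visit, some prepared slots will go unused, and the coordinating centre must issue assignments at short notice. The other items need only text and a small additional table. The sample size does not change.
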